### Randomization

Patients in the trial are allocated to treatment with C1-INH or placebo in a 1:1 ratio, via a confidential interactive web-based algorithm software (Castor EDC, Ciwit B.V., Amsterdam, The Netherlands) using permuted block sized with stratification by study center. Randomization will be performed by the treating neurosurgeon, neurosurgical resident, or research physician after obtaining informed/deferred consent. An automatically generated email will be sent to the pharmacy with information regarding treatment allocation after randomization through Castor EDC.

### Trial interventions

The intervention is the IV administration of C1-INH compared to a placebo (0.9% saline). A single dose of 6000 IU will be administered within 12 h after trauma. Blood samples (2 EDTA, 1 serum, and 1 citrate tube) will be drawn from both patient groups before administration and at 6, 12, 24, 48, 72, and 96 h after administration of C1-INH or placebo in the ICU. Moreover, if an external venticular drain (EVD) is placed as part of standard care to reduce CSF pressure, additional liquor samples will be drawn before administration and 24, 48, 72, and 96 h after administration of C1-INH or placebo in the ICU. All samples will be centrifuged and aliquoted in 500 μl samples as quickly as possible and afterwards stored at − 80 °C. Other interventions are unaltered from local treatment protocols and will include standard of care in both groups. This might include concomitant therapies, such as a decompressive craniectomy. During hospitalization, patients are closely monitored for (serious) adverse events (SAEs). Moreover, health-related questionnaires will be filled out by the patients or proxies at discharge and at 3 months, 6 months, and 12 months after head trauma. A flowchart of the study design is shown in Fig. 2. All study procedures will be performed according to the designated study operating procedures (SOPs).

**Fig. 2 Fig2:**
[figure not shown]
CIAO@TBI study design flowchart. *Abbreviations*: TBI, traumatic brain injury; GCS, Glasgow Coma Scale; HAE, hereditary angio-edema; CSF, cerebrospinal fluid; TIL, therapy intensity level; GOSE, Glasgow Outcome Scale Extended; QoLiBri, Quality of Life after Brain Injury Scale; iPCQ, IMTA Productivity Cost Questionnaire; iMCQ,: IMTA Medical Consumption Questionnaire; SF-36, Short-Form 36; EQ-5D-5L, 5 Level EuroQoL 5-Dimensional Questionnaire

#### Investigational medicinal product

Cinryze (Takeda Development Center Americas, Inc., Lexington, MA) is a nano-filtered C1-inhibitor product, purified from human plasma for fractionation. It is provided as a freeze-dried powder and is reconstituted with 5 ml water at the site by a trained unblinded person. The final concentration of the drug substance is 100 IU/ml, and a total of twelve vials are used for each patient (6000 IU). The total of 60 ml C1-INH will be divided over two syringes and will be infused IV over 1 h. If the patient is randomized for the placebo group, the equivalent amount (60 ml) 0.9% saline will be dosed IV over 1 h.

#### Justification of route of administration and dosage

Administration of the study intervention via the intravenous route is required as subcutaneous dosing yields lower bioavailability and results in a higher incidence of injection site reactions [33]. Moreover, this route is feasible in critically ill patients. The dose of C1-INH or placebo equivalent to be used is based on pharmacokinetics/pharmacodynamics, efficacy, and safety. The 1000/1500-IU dose as prescribed for HAE is enough to inhibit kallikrein-induced bradykinin generation, but not enough to inhibit complement activation (Fig. 1). Safety studies showed that the no observed adverse effect level (NOEL) is 400 U/kg, and 1 unit is necessary to prevent complement activation in 1 ml blood [34]. The efficacy and safety of 6000 IU C1 esterase inhibitor treatment have not yet been tested in TBI patients. Nevertheless, this high dose has been used in critically ill patients before. In a trial in severe sepsis patients, a regime of 6000 IU followed by 3000, 2000, and 1000 IU was used to efficiently block complement activation [30]. This dosage was well tolerated in these critically ill patients, with no drug-related adverse events. Currently, two other RCTs, one evaluating asthma treatment and one focusing on anemia, are recruiting patients with the same dose of 6000 IU Cinryze. Furthermore, other studies have already shown safety of Cinryze at doses of 12,000, 15,000, and 19000 units per patient [31, 35, 36]. A minimal of 6000 IU (which is equivalent to 85 IU/kg for a person weighing 70 kg) is justified to achieve treatment effect without major complications to be expected.

The time window of administration of the investigational product within 12 h after trauma is defined based on the therapeutic window of C1-INH together with the required time to stabilize the critically ill patient and provide the required first urgent interventions. Nevertheless, animal models show that the closer the administration is to the actual trauma, effects are more beneficial, emphasizing the need for early as possible intervention.

### Treatment blinding

Patients, care providers, site investigators, research coordinators, and statisticians will be blinded to treatment allocation. C1-INH and placebo are prepared by an unblinded staff member at each center to provide a ready-to-use solution. This will be a pharmacist or nurse from an independent department, depending on the local site organization, and this person will not be involved in the care of the trial patients and will not discuss trial drug treatment with research staff or other members of the ICU. Preparation and labeling will be done according to the Good Manufacturing Practice Guidelines. The unblinded staff member will provide the C1-INH or placebo in two masked syringes, labeled with a randomization number and infusion rate, to the blinded treatment team. Both the reconstituted C1-INH salutation as the placebo solution are colorless, and provided in identical syringes, therefore maintaining blinding for the treatment team. The trained ICU nurse will infuse the C1-INH or placebo. For safety reasons, emergency unblinding can be performed through Castor EDC.

### Primary endpoints

#### Efficacy: Therapy Intensity Level (TIL) Scale

To measure the direct effect on the mechanism of action of C1-INH, our primary endpoint focuses on a decrease in ICP. ICP has been used as a surrogate endpoint for inflammation and testing of neuroprotective agents in many prematurely halted or failed clinical trials [37]. This might be due to the fact that ICP is an early surrogate marker during TBI but confounded by the modern neuro-ICU practices through escalating interventions (such as decompressive craniectomies (DC)) to immediately mitigate surges in ICP resulting in reduction of its sensitivity, as representing “severity of disease.” Therefore, this trial will focus on the intensity of ICP-targeted therapy based on the Therapy Intensity Level (TIL) Scale [38, 39]. The TIL Scale is designed to integrate all known and relevant ICP directed treatments into a single-summary score and was developed as part of the Interagency Common Data Elements scheme [38]. Since its introduction, the novel TIL Scale has been widely used in neurotrauma research, with excellent inter- and intra-rater reliability with minimal measurement errors [39]. The TIL Scale includes eight ICP treatment modalities each with a certain numerical score. Added together, TIL ranges between 0 and 38 points with a right-skewed distribution. Specifically, TBI patients admitted to the ICU have an average TIL score of 8.2 (SD 3.2), while general trauma patients on the ICU have a score of 2.2 (SD 0.9) [39]. The daily score will be calculated based on the highest score in each item per day (TIL24), to provide a metric on the maximal therapeutic intensity for ICP management for that day. The TIL score will be based on the highest TIL24 during the days an ICP monitor is in place (TILmax) and will be scored by a trained research team, and according to an SOP, thereby optimizing inter- and interrater reliability.

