## Background

Traumatic brain injury (TBI) is a major cause of death and disability around the world. In Europe, over one million traumatic brain injury (TBI) patients are admitted to the hospital yearly, of whom 75,000 people die [1, 2]. This debilitating morbidity leads to enormous societal costs [3]. Therapies and guidelines that have been demonstrated to improve the outcomes after TBI are still limited, especially in the management of severe TBI (s-TBI), defined by Glasgow Coma Scale (GCS) 3–8 [4]. Patients with s-TBI have a high mortality rate, estimated at 30–40% in observational studies [1]. Survivors of s-TBI experience a substantial burden of physical, psychiatric, emotional, and cognitive disabilities that disrupt their lives, their proxy family members, and their social surroundings. Adequate treatment strategies are therefore pivotal. TBI comprises a dynamic pathophysiology that evolves over time, consisting of primary injury after the traumatic hit, followed by systemic disorders which lead to secondary injury [5]. The overshooting inflammatory response and delayed formation of brain edema, mostly seen around the third day after trauma, are characteristics of secondary brain injury, which are in turn related to a complicated clinical course, delayed recovery, late morbidity, and mortality in TBI [6–8].

The complement system forms the first line of defense against microorganisms and is critical in sensing tissue damage. Complement activation can be mediated by three distinct pathways: the classical pathway, the lectin pathway, and the alternative pathway [9]. Multiple experimental studies have identified a pathophysiologic role of the complement system in contributing to posttraumatic neuro-inflammation, disruption of the blood-brain barrier, secondary neuronal damage, and neuronal cell death after TBI [10–14]. Activation of the complement system in s-TBI results in a cascade of events including increased vascular permeability and activation of microglia and astrocytes, ultimately resulting in inflammatory reactions in and around contusion areas [15, 16]. In addition, it triggers a sustained degenerative mechanism of reduced dendritic and synaptic density and inhibited neuroblast migration several weeks after TBI in animal models [17]. In severe TBI patients, elevated complement factors have been found in the serum [18, 19] and in the ventricular cerebrospinal fluid (CSF) directly after initial trauma [20, 21].

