### Trial population and eligibility

All TBI patients presenting to participating hospitals are potentially eligible for this trial. The inclusion criteria are (1) age > 18 years, (2) clinical diagnosis of TBI with GCS < 13 on admission (with visible intracranial pathology on CT), and (3) invasive intracranial pressure monitoring by intra-parenchymatous transducer or ventricular catheter placement and management of increased ICP for at least 24 h. The exclusion criteria are (1) a clear, non-traumatic cause of low GCS on admission (e.g., toxic or cardiac cause); (2) not expected to survive more than 24 h after admission with the decision to abstain from aggressive treatment and induce palliative care; (3) brain death on arrival in the participating centers; (4) severe pre-trauma disability, defined as being dependent on other people; (5) known prior history of sensitivity to blood products or C1-INH; (6) patients with a history of hereditary angioedema (if known at admission); (7) patients with a history of thrombosis (deep vein thrombosis, cerebral venous sinus thrombosis, or pulmonary embolism) (if known at admission); and (8) patients that are pregnant (if known at admission).

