
### Sample size

To detect a between-group difference in the TIL Scale of 2.2, with 90% power and 0.05 (two-sided) significance level, a total of 106 patients are required. Calculations were based on the anticipated mean of 8.2 and standard deviation 3.2 of the novel TIL in TBI patients admitted to the ICU [38]. The patient group treated with C1-INH is estimated to have an average TIL of 6 [39, 51]. Both treatment groups will include 53 patients to power the trial and to account for withdrawal and loss to follow-up (approximately 10%). With this sample size, a difference of 2.2 on the TIL scale can be detected, which is clinically relevant as it corresponds to one medium level of intervention (such as CSF drainage or mannitol treatment) less to control ICP indicating a significant treatment effect. As no minimal clinically important difference (MCID) for the TIL scale is defined in the literature, we will adhere to this shift of 2.2 points on the right-skewed scale.

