### Ethics

The study protocol was designed in accordance with the ethical principles in the Declaration of Helsinki and the regional regulations, and the principles of Good Clinical Practice. Participants will be assessed for eligibility by the neurosurgical resident or research physician when an ICP monitor is placed within 12 h from trauma. Within this time frame, informed consent must also be obtained. Ideally, the treating physician will obtain informed consent from the patient. As the enrolled subjects will lack capacity to consent due to their level of consciousness at presentation, informed consent can be obtained within 12 h after trauma by a legally authorized representative of the patient. As TBI mostly occurs outside the domestic situation, family members are rarely available during the first hours after trauma [57]. Therefore, the treating physician will take responsibility for including the patient using “deferred proxy consent” if the following condition are met and documented: (1) the patients is in a potentially life-threatening situation and (2) the patient meets the eligibility criteria for trial entry. As there is a potential benefit with the administration of C1-INH and an urgent therapeutic timeframe of 12 h, deferred consent is justified in these patients [58–60]. Following enrollment via deferred consent, informed consent should still be obtained by a legal representative within 7 days after admission. Furthermore, the patient must agree to further participate in the study when mental capacity is regained. When consent for study continuation is provided, already collected data can be used. When study continuation is refused, already collected data can still be used when patients and/or proxies do not use their right to refuse this. Patients or proxies should always be informed about their right to refuse the use of obtained data. A team of dedicated research nurses and physicians are trained to perform the specific informed consent and randomization procedures. Moreover, a 24/7 study consultation telephone number can be reached to help with problems or questions during the study.

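### As written, the TILmax window opens before the study drug is given, so pre-infusion therapy can set the primary endpoint and cost power; its end at death or monitor removal is a smaller, secondary problem

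*Protocol article*

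**What the plan says.** The section on the Therapy Intensity Level Scale builds the endpoint in two steps. First comes the daily score: "The daily score will be calculated based on the highest score in each item per day (TIL24". Then comes the patient's score: "The TIL score will be based on the highest TIL24 during the days an ICP monitor is in place (TILmax". Neither step mentions the time of infusion, and the window has no fixed length.

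Three other sections fix the order of events:

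- Trial population and eligibility requires "invasive intracranial pressure monitoring by intra-parenchymatous transducer or ventricular catheter placement and management of increased ICP for at least 24 h".
- Ethics says: "Participants will be assessed for eligibility by the neurosurgical resident or research physician when an ICP monitor is placed within 12 h from trauma".
- Trial interventions says: "A single dose of 6000 IU will be administered within 12 h after trauma". The dosage justification explains that this interval leaves time to stabilise the patient and carry out the first urgent procedures.

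Statistical analysis specifies a linear model for TILmax, adjusted for age, GCS and pupillary reactivity, in all randomised patients. Pre-dose TIL is not a covariate. GOSE at 6 months is tested only if TIL is significant. Sample size rests on the "anticipated mean of 8.2 and standard deviation 3.2 of the novel TIL", a treated mean of 6, 90% power and 53 patients per arm with about 10% loss.

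Background places delayed oedema mostly around the third day and states: "Patients with s-TBI have a high mortality rate", at 30–40% in observational studies.

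**The concern.** An efficacy score should reflect what happens after treatment starts. Here the window opens at monitor placement, which comes before randomisation and infusion, and the daily score takes the worst value of each item over the whole day. Intensive ICP therapy in the hours before infusion can therefore become the patient's TILmax. With an average over days, later benefit would still show. With a maximum, it would not.

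The window also ends at events that occur after randomisation, namely death, withdrawal of care or removal of the monitor. A patient who dies before the expected oedema peak has had fewer days in which to reach a high score, and the linear model would read a low score as a good result.

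TIL is the gatekeeper for GOSE and the endpoint on which success is declared. Lost sensitivity here is not recovered elsewhere in the testing sequence.

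**Working it through.** **1. The plan's own figure.** Inputs from Sample size: difference 2.2, SD 3.2, two-sided 0.05, power 0.90.

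Normal approximation: n per arm = 2 × (1.960 + 1.282)² × 3.2² / 2.2² = 44.5, rounded up to 45. The t-test version gives 45.4, rounded up to 46. With 10% loss, 46 / 0.9 = 51.1, so 52 per arm or 104 in total. The stated 106 is within two patients of this, so the sample size follows from its own inputs.

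Evaluable patients after 10% loss: 53 × 0.9 = 47.7, taken as 48 per arm. Power for 2.2 with SD 3.2 is then 0.92.

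**2. Effect of the pre-dose window.** Scored as written, TILmax = max(pre-dose TIL, post-dose maximum). I simulated this with:

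- post-dose maximum with mean 8.2 (control) and 6.0 (C1-INH), SD 3.2, taken from the article on the assumption that the planned gap belongs to the post-dose maximum;
- pre-dose TIL with the same distribution in both arms, mean 2 to 6, SD 2.5 to 3, correlation 0.3 to 0.7 with the post-dose maximum (all assumed, since the article gives none of these);
- scores bounded at 0 and 38, and 48 patients per arm.

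Power uses the SD of the resulting maximum, not 3.2. Taking a maximum shrinks the spread as well as the difference.

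| Assumed pre-dose mean | Remaining difference | SD of TILmax | Power, 48 per arm |
|---|---|---|---|
| none (undiluted) | 2.2 | 3.2 | 0.92 |
| 2 | 2.0–2.1 | 3.0–3.1 | 0.89–0.91 |
| 3 | 1.9–2.1 | 3.0–3.1 | 0.87–0.90 |
| 4 | 1.75–2.0 | 2.9–3.1 | 0.83–0.88 |
| 5 | 1.6–1.8 | 2.8–3.0 | 0.76–0.83 |
| 6 | 1.35–1.5 | 2.7–3.0 | 0.65–0.71 |

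At a pre-dose mean of 6, half of treated patients have a pre-dose score at or above their whole post-dose maximum. That row is an extreme.

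**3. Effect of early truncation.** If early death lowers TILmax by g points and the arms differ by q in the proportion of early deaths, the mean difference shifts by g × q. With g = 2 to 4 and q = 0.05 to 0.10 (both assumed), the shift runs from 2 × 0.05 = 0.1 to 4 × 0.10 = 0.4 points, in favour of the arm with more early deaths. For scale, significance at 48 per arm needs about 1.985 × 3.2 × √(2/48) = 1.3 points.

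**4. Value of a baseline covariate.** Adjusting for a pre-dose score with correlation r multiplies the residual variance by 1 − r². At r = 0.5 that is 1 − 0.25, a 25% reduction, before allowing for overlap with age, GCS and pupils.

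**The case against.** The article is a condensed account and says TIL is scored under an SOP that is not shown. That SOP may set when day 1 begins, and an analysis plan may say how death is handled. This is fair: one cannot assert that pre-dose therapy will be counted. But the article does state the window, by monitor days, and that wording admits pre-dose therapy. The model's covariates are also stated, without pre-dose TIL.

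The dilution may be small. Infusion falls within the first 12 h, whereas oedema is expected around day 3, so many maxima should arise after dosing. This stands, and it points to the upper rows of the table. The 2.2-point gap might also have been meant for the endpoint exactly as scored, in which case some dilution is already built in. The article does not say. Nor do the simulations credit the gain from adjusting for age, GCS and pupils.

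A reader might infer that truncation by death could make a harmful drug look beneficial. The documents do not support that. A patient dying of refractory ICP may already have reached maximal therapy, so the direction is unknown. The 30–40% is overall mortality in severe TBI, not deaths during monitoring. The trial also admits GCS 9–12 and excludes some patients not expected to survive 24 h. Mortality is a secondary endpoint and is reviewed unblinded by the DSMB.

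A reader might also suspect that 3.2 is not the SD of a TILmax and that power is lower for that reason. That depends on a cited source not at hand, so it is not part of this point.

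**Conclusion.** The point holds as a weakness in the endpoint definition. As written, therapy given before infusion can determine the primary endpoint, and the model does not adjust for it. Because randomisation balances pre-dose therapy, the consequence is a difference pulled towards zero and reduced power. A reader might take it as bias in favour of C1-INH, but nothing in the document supports that.

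The size is conditional. If the planned 2.2 points refer to the post-dose maximum, power at 48 per arm falls from 0.92 to 0.87–0.91 for assumed pre-dose means of 2–3, and to about 0.65–0.88 for means of 4–6. The article's own timing of oedema favours the small end. Lower power figures for these scenarios arise only if the SD is held at 3.2 while the difference shrinks, which is inconsistent with taking a maximum.

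Truncation by death or end of monitoring is secondary: uncertain in direction, and about 0.1–0.4 points under the assumed imbalances. The sample size of 106 is not in error on its stated inputs.

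**What to change.** 1. Define TILmax as the highest score from the start of infusion onwards, splitting the first day at the infusion time. State this in the endpoint definition and in the scoring SOP.
2. Record TIL from before infusion as a baseline value, and add it to the linear model alongside age, GCS and pupillary reactivity.
3. Prespecify one sensitivity analysis of TILmax, for example rank-based, in which death or withdrawal of care during monitoring counts as the worst outcome.

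The cost is some extra chart scoring to divide day 1, one additional covariate and one additional analysis. Treatment, dose and sample size stay as they are. If the SOP already starts scoring at infusion, the first step reduces to saying so in the endpoint definition.

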#### Efficacy: GOSE at 6 months

The co-primary efficacy endpoint will be the Extended Glasgow Outcome Scale (GOSE) at 6 months after trauma [40]. The GOSE [41], derived from its precursor the GOS [42], defines disability on an 8-point scale and incorporates emotional and cognitive disturbances affecting disability. A score of 5 or more indicates functional independence. The GOSE is designed as a structured interview and can also be applied through telephone [43] and e-mail or postal [44]. Two research nurses or researchers will independently grade the outcomes based on the GOSE in each patient according to the standardized approach. Disagreements will be resolved by consensus between them or by consultation of a third, independent investigator.

